## Methods

### Sample size determination

The sample size was estimated using G*Power version 3.1 (Heinrich Heine University Düsseldorf, Germany) based on the composite sarcopenia Z-score. A previous comparable trial reported a large intervention effect on sarcopenia Z-score (SMD = 1.40) [31]. With 80% power, a Bonferroni-adjusted two-sided α of 0.0167, and ANCOVA adjustment for baseline sarcopenia Z-score, 16 completers per group are required in an individually randomized design, corresponding to 64 completers in total. To account for cluster randomization at the residential-building level, the sample size was inflated using the adjusted design effect formula, DE = 1 + [m (1 + CV^2^) − 1] × ICC. Based on a recent cluster-randomized trial in senior care facilities using Short Physical Performance Battery (SPPB) as the primary outcome, an intracluster correlation coefficient (ICC) of 0.025 was adopted [32]. A CV of 0.30 was used to account for anticipated variation in cluster size [33]. With 19 clusters, these assumptions yielded an adjusted design effect of approximately 1.12. After allowing for a 30% dropout rate, the sample size was increased to 104 participants, targeting approximately 26 participants per group. Cluster effects will be further addressed using mixed-effects models with random intercepts for residential building and participant.

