### Outcome assessment

Outcome assessments are scheduled to evaluate both short-term intervention effects and the maintenance of longer-term benefits. With the exception of biospecimen collection, the outcomes will be assessed at baseline, weeks 12, 24, and 48, and again at 1-year and 2-year post-intervention follow-up. HG will additionally be measured every 4 weeks during the intervention period to capture more continuous changes in muscle strength, whereas biospecimens will be collected at baseline and week 48 only. The full assessment schedule is summarized in Table 1.

**Table 1 Tab1:** Schedule of study assessments

Measure	Screening	Baseline	Intervention												Follow-up	
		**Week 0**	**Week 4**	**Week 8**	**Week 12**	**Week 16**	**Week 20**	**Week 24**	**Week 28**	**Week 32**	**Week 36**	**Week 40**	**Week 44**	**Week 48**	**Year 1**	**Year 2**
Primary outcomes																
Sarcopenia Z-score	** × **	** × **			** × **			** × **						** × **	** × **	** × **
Components																
ASMI	** × **	** × **			** × **			** × **						** × **	** × **	** × **
HG	** × **	** × **	** × **	** × **	** × **	** × **	** × **	** × **	** × **	** × **	** × **	** × **	** × **	** × **	** × **	** × **
SPPB	** × **	** × **			** × **			** × **						** × **	** × **	** × **
Secondary outcomes																
TUG		** × **			** × **			** × **						** × **	** × **	** × **
PA level		** × **			** × **			** × **						** × **	** × **	** × **
sEMG		** × **			** × **			** × **						** × **	** × **	** × **
Balance function		** × **			** × **			** × **						** × **	** × **	** × **
Sample collection		** × **												** × **		
Questionnaires		** × **			** × **			** × **						** × **	** × **	** × **
Clinical events		** × **			** × **			** × **						** × **	** × **	** × **
Care-dependency		** × **			** × **			** × **						** × **	** × **	** × **

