All assessments will be conducted by trained research staff using standardized procedures, and outcome assessors will remain blinded to group allocation. To minimize participant burden, assessments will be arranged on residents’ residential floors whenever feasible. Portable and low-risk assessments will be conducted in residents’ rooms, whereas physical performance and device-based assessments will be completed in nearby familiar spaces under safety supervision. Non-time-varying or historical variables will be collected at baseline only. Rest breaks will be provided, and assessments may be split across short sessions, deferred, shortened, or omitted if participants experience fatigue, discomfort, or safety concerns. When the full assessment battery cannot be completed, primary outcome components and safety-related assessments will be prioritized, followed by key functional outcomes; exploratory mechanistic assessments, including sEMG, balance-board testing, and biospecimen collection, will be conducted only when safe and tolerated. Reasons for incomplete assessments will be documented.

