### Statistical analysis

All analyses will follow the intention-to-treat (ITT) principle, including all randomized participants in their assigned groups regardless of adherence or withdrawal [75]. Data will be stored in a password-protected database and managed by designated research staff. Analyses will be performed by an independent statistician using R software (R Foundation for Statistical Computing, Vienna, Austria).

Baseline characteristics will be summarized using descriptive statistics. Continuous variables will be presented as mean ± SD or median [IQR], as appropriate, and categorical variables as frequencies and percentages. Baseline balance across groups and clusters will be descriptively assessed.

Primary and secondary continuous outcomes will be analyzed using linear mixed-effects models, with fixed effects for group, time, and group-by-time interaction, and adjustment for the baseline value of the corresponding outcome and relevant covariates where appropriate. Random intercepts for residential building clusters and participants will be included to account for cluster randomization and repeated measurements. The main intervention effect will be estimated from the group-by-time interaction, with Week 48 as the primary endpoint. Bonferroni-adjusted post-hoc comparisons will be conducted where appropriate. Binary or categorical outcomes, including adverse events, will be analyzed using generalized linear mixed models. Long-term clinical events and care-dependency records will be summarized descriptively by group, with exploratory cluster-adjusted analyses conducted if event numbers permit.

Model assumptions will be assessed using residual diagnostics, and transformations or robust methods will be considered if needed. Missing outcome data will be handled using multiple imputation under the missing-at-random assumption. Sensitivity analyses will compare the intention-to-treat results with per-protocol and complete-case analyses. Effect sizes will be reported as standardized mean differences for continuous outcomes and odds ratios for binary outcomes. Statistical significance will be set at a two-sided α = 0.05.

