A comprehensive assessment framework will be applied to capture both clinical effectiveness and underlying mechanisms of action. In contrast to prior studies relying on single-domain endpoints [85, 86], the primary outcome is a composite Z-score integrating muscle mass, strength, and physical performance, thereby providing a continuous measure of sarcopenia severity. To account for potential compensatory reductions in daily activity [87], accelerometer-based monitoring will be implemented at multiple time points to quantify overall activity changes and examine their moderating effects [87, 88]. The assessment strategy is further extended to include surface electromyography and center of pressure measures of standing balance in order to elucidate neuromuscular adaptations associated with different exercise modalities [89]. In particular, saliva-derived DNA will be utilized for telomere length determination and methylation analyses, providing accessible biomarkers for aging-related molecular adaptations to exercise [90–92].

Several limitations must be acknowledged. While the SCOPE study will be conducted in the largest nursing home facility in the region, the single-centre design may affect the generalisability of the results. Because reliable ICC and effect-size estimates for the proposed composite sarcopenia Z-score in oldest-old nursing home residents are limited, the sample-size calculation should be interpreted as a pragmatic planning estimate. The study may be underpowered to detect small between-group effects, and the observed ICCs and cluster sizes will be reported to inform future definitive trials. The 48-week intervention period, while necessary for assessing long-term effects and accounting for seasonal variation [93], could increase the risk of attrition due to health deterioration, institutional transfers, or temporary facility closures. To mitigate these challenges, the protocol incorporates adaptive strategies such as intervention period extension, home-based exercise guidance, and optional live-streamed sessions to support continued participation during absences. Additionally, to better simulate real-world staff turnover and resident mobility, the recruitment in predefined waves may be implemented as needed. This flexible approach ensures that the trial can adapt to the dynamic nature of nursing home environments.

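### Missing outcomes are imputed under missing at random with no exception for death, and neither missing-data sensitivity analysis can show what happens if that assumption fails

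*Protocol article*

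**What the plan says.** All points are in the protocol article.

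- **Analysis set (Statistical analysis).** Intention to treat, "including all randomized participants in their assigned groups regardless of adherence or withdrawal".
- **Missing outcomes (same section).** "Missing outcome data will be handled using multiple imputation under the missing-at-random assumption". No exception is made for death or for residents who cannot be tested.
- **Checks (same section).** "Sensitivity analyses will compare the intention-to-treat results with per-protocol and complete-case analyses". The other sensitivity analyses in the article concern baseline imbalance (Randomization and blinding) and contamination (Discussion), not missing data.
- **Target (same section).** "The main intervention effect will be estimated from the group-by-time interaction, with Week 48 as the primary endpoint". Under Outcome assessment, nearly all outcomes are measured "again at 1-year and 2-year post-intervention follow-up" as well.
- **Expected losses.** The sample size is set "After allowing for a 30% dropout rate". The Discussion says the long intervention "could increase the risk of attrition due to health deterioration, institutional transfers, or temporary facility closures". Outcome assessment says that "assessments may be split across short sessions, deferred, shortened, or omitted if participants experience fatigue, discomfort, or safety concerns".
- **Death (Secondary outcomes, Statistical analysis).** All-cause mortality is recorded to two years after the intervention, but long-term clinical events are summarized descriptively and are not linked to the primary analysis.

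**The concern.** MAR means that, given what has been observed, missingness does not depend on the value that was not seen. Several reasons the protocol gives for missing data point towards poor unseen values: deteriorating health, fatigue and safety concerns during testing. Part of that decline will be visible at earlier visits, and part may not be.

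Death is a different problem. Grip, SPPB and muscle mass do not exist after death, so there is no missing value to recover. Under the unrestricted rule, the Week 48 effect and especially the 1- and 2-year results could rest partly on values created for residents who have died.

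The two planned comparisons do not expose either problem. For missing outcomes, complete-case analysis needs an assumption at least as strong as MAR. Per-protocol analysis answers a question about a different population. If it is defined by attendance, it selects residents only in the exercise arms, because controls have no study sessions. Agreement between these analyses and the main one could be read as robustness when all of them share the same bias.

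**Working it through.** **1. The plan's dropout figure.** Inputs from Sample size determination: 16 completers per group, ICC 0.025, CV 0.30, 19 clusters, 30% dropout, total 104.

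- Mean cluster size: 104 / 19 = 5.47.
- Design effect: 1 + (5.47 × 1.09 − 1) × 0.025 = 1.124, which matches the stated 1.12.
- 16 × 1.124 = 17.99, rounded up to 18 per group. 18 / 0.70 = 25.7, rounded up to 26 per group, or 104 in total.

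The stated 104 reproduces, so 30% missing is a working input of the plan: 8 of 26 per arm, and 0.30 × 104 = about 31 residents overall.

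**2. Bias when MAR fails.** Let f be the missing fraction in an arm and δ the amount, in SD, by which its missing values are worse than MAR predicts. T is an exercise arm and C is control. Higher Z-scores are worse, so

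overstatement of benefit = f_T × δ_T − f_C × δ_C.

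The δ values and arm-specific fractions are assumptions; the documents give only the overall 30%.

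| f_T, f_C | δ_T, δ_C | Overstatement (SD) |
|---|---|---|
| 0.30, 0.30 | 1.0, 1.0 | 0 |
| 0.30, 0.30 | 0.5, 0 | +0.15 |
| 0.30, 0.30 | 1.0, 0 | +0.30 |
| 0.30, 0.30 | 0, 0.5 | −0.15 |
| 0.40, 0.20 | 1.0, 1.0 | +0.20 |

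Against the planning effect of 1.40, 0.15 is 11% and 0.30 is 21%.

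**3. Can the complete-case comparison reveal this?** A simulation used 1,500 trials per scenario, two arms of 26, about 30% missing and an assumed baseline correlation of 0.6. It compared multiple imputation under MAR (predictors: arm and baseline) with complete-case ANCOVA. Entries are estimated benefit in SD.

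| Missingness depends on | True 0: MI / complete-case | True 1.40: MI / complete-case |
|---|---|---|
| Baseline only (MAR) | −0.008 / −0.006 | 1.393 / 1.392 |
| Unseen outcome, both arms alike | −0.009 / −0.008 | 1.393 / 1.392 |
| Unseen outcome, exercise arm only | 0.257 / 0.256 | 1.656 / 1.659 |
| Unseen outcome, control arm only | −0.257 / −0.259 | 1.157 / 1.157 |

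The two methods agree in every row, including the rows where both are wrong by about a quarter of an SD. The imputation used no interim measurements. With them the two estimates could separate, but the gap would show what the observed data explain, not the part that violates MAR.

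**4. Deaths.** The documents give no mortality rate, so the number of residents affected cannot be derived from them.

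**The case against.** The case on the other side has real force in five places.

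- **Death.** A reader might infer that the protocol states it will impute outcomes for residents who died. It does not say so. That follows only from combining the analysis set of all randomized residents with an imputation rule that has no exception. The full protocol or an SAP, neither shown, may restrict it.
- **SPPB.** A reader might infer that a resident too weak for an SPPB task is imputed from those who could do it. The article scores each component from 0 to 4 by standard criteria, which may already give inability a 0. That inference is not supported.
- **MAR is not refuted by health-related dropout.** All components are measured at weeks 12 and 24, and grip every 4 weeks. Decline seen there can be absorbed if the imputation uses it. The simulation leaves this out, so its 0.26 SD illustrates the mechanism and does not forecast the trial's bias.
- **Mitigation exists.** Primary components are prioritized when testing is cut short, reasons for incomplete assessments are documented, residents who stop exercising are encouraged to stay in follow-up, and deaths are recorded and summarized.
- **The article never calls the two comparisons tests of MAR.** They are legitimate supplementary analyses.

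These points narrow the finding but do not remove it. The article itself fixes both the assumption and the missing-data comparisons, and neither comparison addresses the departure that its own reasons for missingness make plausible.

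**Conclusion.** The point holds as a cheap and worthwhile correction. Missing outcomes are imputed under MAR with no stated exception for death, and nothing listed shows how the result would change if MAR failed.

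A reader might conclude that the exercise effects will be overstated. The documents do not support a direction. Overstatement needs more, or worse, unseen outcomes in an exercise arm than in control; the reverse pattern understates benefit. At 30% missing, the Week 48 effect moves by 0.30 SD for each 1 SD by which one arm's missing values differ from the MAR prediction. It moves by about zero if the arms share the same mechanism and missing fraction. A difference between arms is possible because only the exercise arms have sessions, attendance incentives and recognition, but the protocol gives no evidence on its size.

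The size rests on the plan's 30% dropout and on assumed shifts. The 1- and 2-year results are more exposed to deaths because more time has passed, by an amount the documents do not allow to be calculated.

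**What to change.** In the Statistical analysis section:

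1. State that outcomes are not imputed after death. Estimate the effect in residents alive at the visit and report deaths by arm beside it, since survivors are no longer a randomized comparison if mortality differs between arms.
2. Impute the three components rather than their sum. Use the 4-weekly grip and the week 12 and 24 values as auxiliary variables, and account for building in the imputation model.
3. Keep complete-case and per-protocol analyses as supplementary. Add a delta-adjusted or control-based imputation with arm-specific shifts as the check on MAR, and report the tipping point at which the Week 48 conclusion changes.

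The cost is revised wording, some extra programming and possibly a less favourable robustness statement. No new data are needed: deaths, reasons for incomplete assessments, interim visits and repeated grip are already to be collected. The change is most credible if made before outcome data are analysed.

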## Discussion

Sarcopenia presents an increasingly critical challenge to healthy ageing, with notably higher prevalence and more severe functional impairments among nursing home residents compared to community-dwelling older adults [76–78]. This vulnerable population experiences significant limitations in physical function, which directly compromise quality of life [5]. While exercise interventions are widely recognised as effective in sarcopenia management, the majority of existing evidence comes from highly controlled trials conducted in community settings [10, 11, 79–82]. This gap in evidence limits our understanding of how these interventions perform in real-world residential care environments.

To address this gap, the SCOPE study focuses on three exercise modalities: modified Baduanjin, resistance training, and their combination. These interventions were selected based on strong evidence from large-scale meta-analyses, which confirm their efficacy in improving sarcopenia-related outcomes [7, 22]. To ensure time-matched comparisons, all intervention groups will receive the same total session duration and weekly frequency. A cluster-randomised design at the residential building level will be employed to align with routine care workflows and minimize intervention contamination, as individual randomization within the same building could lead to cross-contamination between participants and complicate intervention management in nursing home settings. Although residential-building cluster randomization can reduce contamination between trial arms [83], residual contamination cannot be completely ruled out because all clusters are located within one nursing home, where interactions among residents and caregivers occur as part of routine care [84]. Separate building-based delivery, group-specific scheduling and materials, caregiver assignment, and documentation of additional exercise or cross-group exposure are intended to reduce and monitor this risk. Potential contamination will be considered when interpreting between-group effects and explored in sensitivity analyses where data permit [39]. By implementing a caregiver-led, video-assisted delivery model, the SCOPE study is designed to maximise its relevance to routine practice. This approach integrates existing facilities, a flexible supervision schedule, and an adherence incentive system, which will allow assessment of both intervention effectiveness and feasibility, scalability, and sustainability within nursing home settings.

A comprehensive assessment framework will be applied to capture both clinical effectiveness and underlying mechanisms of action. In contrast to prior studies relying on single-domain endpoints [85, 86], the primary outcome is a composite Z-score integrating muscle mass, strength, and physical performance, thereby providing a continuous measure of sarcopenia severity. To account for potential compensatory reductions in daily activity [87], accelerometer-based monitoring will be implemented at multiple time points to quantify overall activity changes and examine their moderating effects [87, 88]. The assessment strategy is further extended to include surface electromyography and center of pressure measures of standing balance in order to elucidate neuromuscular adaptations associated with different exercise modalities [89]. In particular, saliva-derived DNA will be utilized for telomere length determination and methylation analyses, providing accessible biomarkers for aging-related molecular adaptations to exercise [90–92].

Several limitations must be acknowledged. While the SCOPE study will be conducted in the largest nursing home facility in the region, the single-centre design may affect the generalisability of the results. Because reliable ICC and effect-size estimates for the proposed composite sarcopenia Z-score in oldest-old nursing home residents are limited, the sample-size calculation should be interpreted as a pragmatic planning estimate. The study may be underpowered to detect small between-group effects, and the observed ICCs and cluster sizes will be reported to inform future definitive trials. The 48-week intervention period, while necessary for assessing long-term effects and accounting for seasonal variation [93], could increase the risk of attrition due to health deterioration, institutional transfers, or temporary facility closures. To mitigate these challenges, the protocol incorporates adaptive strategies such as intervention period extension, home-based exercise guidance, and optional live-streamed sessions to support continued participation during absences. Additionally, to better simulate real-world staff turnover and resident mobility, the recruitment in predefined waves may be implemented as needed. This flexible approach ensures that the trial can adapt to the dynamic nature of nursing home environments.

Through its cluster-randomised design, the SCOPE study is expected to establish a practical framework for implementing evidence-based exercise programmes in institutional care settings. The findings are expected to inform the development of standardised exercise guidelines for sarcopenia management in long-term care facilities and guide evidence-based decisions regarding staffing and resource allocation. More broadly, the SCOPE study is expected to exemplify the integration of research and practice, providing a scalable model that bridges the gap between controlled efficacy trials and routine care delivery, offering valuable insights for future research aimed at integrating complex interventions into real-world healthcare systems.

